The European Guidelines and the 2019 ACC/AHA Guideline acknowledge that special considerations are required when prescribing lipid-lowering agents in older people because exposure to higher doses (or higher potency) may not increase life expectancy but may increase the risk of adverse effects. Assessment of risk status and a clinician–patient discussion of risk are needed to decide whether to initiate or continue statin treatment.

Statins represent one of the largest pharmaceutical industry markets in France; in 2014, around 5 million people were treated with statins, representing a total cost of 550 million euros. People 75 years and older represented 9.3% of the total population in 2019 [5]. We estimate that around 25% of these people are treated with statins, including around 40% in the context of primary prevention (target population over 500,000 people in France).

Given the absence of formal evidence of efficacy, and the high level of side effects, the risk/benefit ratio of primary prevention with statins in elderly patients has not been established. With no controlled studies to validate the benefits of statins in this population, there is some controversy in the literature about their use in this age group [6–16].

One previous trial implied that stopping statin medication therapy is safe and may be associated with a number of benefits, including improved quality of life (QOL) among patients with advanced life-limiting illness [17].

We postulate that statin cessation in patients older than 75 years, when prescribed for primary prevention of CV events, will be safe and may improve QOL through the absence of adverse effects, and lower the costs for the French National Health Insurance System.

The two main objectives of this study are therefore to assess the cost-effectiveness, in real-life use, of statin cessation in patients over 75 years old being treated for primary prevention of CV events and to examine the non-inferiority of statin cessation in terms of all-cause mortality in patients older than 75 years.

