### Randomization

Randomization is being carried out centrally using the e-CRF on the day of the visit for participant inclusion, after the participant has signed the consent form. Participants are considered enrolled in the trial when randomized.

The randomization is unbalanced, with a 5:4 ratio in favour of the statin-continuation group to take into account a 20% risk that patients allocated to the statin continuation group will stop statins after randomization for any reason (side effects, patient’s decision, physician’s decision). The allocation sequence was elaborated using computer-generated random numbers, and was not stratified. To reduce predictability of a random sequence, we used blocks of varying size. A document describing the randomization procedure is kept confidential within the Clinical Epidemiology Unit.

Taking statins or discontinuing statins will not require alteration to usual care pathways (including use of any medication) and these will continue in both trial arms. Participants in the statin discontinuation group who experience a new vascular event will be allowed to restart statins at the discretion of the investigator and according to good clinical practice.

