### Outcome measures

#### Economic endpoints

The cost-effectiveness of the statin cessation strategy compared to continuation of statins will be estimated based on the incremental cost per quality-adjusted life year (QALY) gained at 36 months, from the perspective of the French healthcare system. QALYs will be measured using the Euro-QOL five-dimension, three-level (EQ-5D-3 L) questionnaire at inclusion and at each follow-up visit [18]. This questionnaire has been validated in the French population.

Healthcare resources and costs will be extracted from the French Administrative Health Care Database (Système National des Données de Santé, SNDS) by a merging procedure, operated by the French National Health Insurance Fund and using data from the SITE trial. The SNDS gathers all reimbursement data for 98.8% of the French population [19]. The time horizon of the study (36 months) implies a discounting of costs and outcomes. In accordance with the methodological economic guidelines of the French National Health Authority (Haute Autorité de Santé, HAS), we will apply a 4% discount rate.

Following cost-effectiveness analysis (CEA), budget impact analysis (BIA) will provide useful information about the sustainability of the statin cessation strategy if it were applied to the entire French healthcare system. It will consider outpatient costs, hospital costs, medical and non-medical costs induced or avoided by stopping statins, and all budgetary implications related to changes in health management and/or health status improvement. The difference between induced and avoided costs will provide the net benefit to the healthcare system of widespread adoption of the statin cessation strategy for primary prevention among elderly individuals in France.

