### Statistical methodology

In the non-inferiority analysis, the bilateral 95% confidence interval (CI) for the between-group difference in the 3-year mortality rate will be estimated. Considering < 5% change as clinically non-significant, we will consider non-inferiority demonstrated only if the 95% CI upper bound of the 3-year mortality difference between the two groups is < 5%. This analysis will primarily be performed according to an under-treatment principle. Formally, patients who do not receive the trial treatment as planned in the protocol will be excluded from the analysis. An intention-to-treat analysis will also be performed with the aim of maintaining the initial effect of randomization. The “missing = failure” strategy (failure being defined as death) will be used in the non-inferiority analysis.

Secondary clinical analyses will be conducted according to the intention-to-treat principle: all randomized patients will be analysed in the group to which they were initially randomized, and all of their data will be used regardless of eventual treatment changes during the study. As economic analysis is not based on statistical tests, no adjustment of the α-level is needed to deal with multiple comparisons. In all analyses, *p* < 0.05 will be taken to indicate statistical significance. A statistical team will analyse all data independently of the investigator.

The economic analysis will also be conducted according to the intention-to-treat principle. First, the point estimate of the incremental cost/utility ratio and its bootstrap 95% CI will be calculated. We will then estimate the incremental net monetary benefit (INMB) adjusted for potential confounding factors (adherence to statins at baseline, treatment duration, and particular statin dosage) using multiple linear regression models. Acceptability curves will then be plotted. The value of information will also be examined according to the principles proposed by Claxton [20].

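### The economic analysis adjusts only for statin-use variables and leaves out pre-randomisation healthcare cost, which costs precision in the incremental cost but not validity

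*Protocol article*

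**What the plan says.** Cost-effectiveness is a main objective in the protocol article (Background): "The two main objectives of this study are therefore to assess the cost-effectiveness, in real-life use, of statin cessation". On the source of costs, the Economic endpoints section says: "Healthcare resources and costs will be extracted from the French Administrative Health Care Database". On coverage it says: "The SNDS gathers all reimbursement data for 98.8% of the French population". It does not state what period will be extracted for each patient.

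The analysis is set out under Statistical methodology. The analysis set is fixed there: "The economic analysis will also be conducted according to the intention-to-treat principle". The first estimate is unadjusted as far as the text shows: "the point estimate of the incremental cost/utility ratio and its bootstrap 95% CI will be calculated". The second is the INMB, "adjusted for potential confounding factors (adherence to statins at baseline, treatment duration, and particular statin dosage) using multiple linear regression models". Acceptability curves and a value-of-information analysis follow.

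On allocation, the Randomization section says: "The allocation sequence was elaborated using computer-generated random numbers, and was not stratified".

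No expected saving, cost SD or target precision for costs is given. The only cost figure that helps with scale is in the Background: in 2014, "around 5 million people were treated with statins, representing a total cost of 550 million euros".

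**The concern.** The article accepts covariate adjustment for the INMB and names the covariates. All three describe how the patient used statins before or at entry. None directly measures how much healthcare the patient consumes, which is what total cost measures. A patient's own cost before randomisation is the natural baseline value of a cost outcome, and the linkage already planned could plausibly provide it.

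Precision matters here for two reasons that the article itself supplies. It says that the economic analysis does not rest on statistical tests, so the point estimate and its spread carry the conclusion. It also plans a value-of-information analysis, whose result depends directly on the uncertainty in the INMB. Variance that a baseline covariate could explain is otherwise reported as uncertainty about the strategy.

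**Working it through.** **The article's own figures.** The sample size was set for mortality. With 15% in both arms, a 5-point margin, one-sided 2.5% and 90% power, n per arm = (1.960 + 1.282)² × 2 × 0.15 × 0.85 / 0.05² ≈ 1,072, against 1080 stated. The continuation arm is 1080 / 0.8 = 1350, as stated. There is no corresponding figure for costs to reproduce.

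**A yardstick for the drug saving** (Background; 4% discount rate from Economic endpoints).
- Per treated person: 550 million / 5 million = EUR 110 a year.
- Over 3 years: EUR 330 undiscounted, or 110 + 110/1.04 + 110/1.04² = EUR 317 with the first year undiscounted.
- If the 20% of the continuation arm expected to stop did so at once: 0.8 × 317 = EUR 254.

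This is a 2014 average over all ages and covers the drug only. It gives scale and is not the trial's expected incremental cost.

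**SE of the cost difference.** SE = SD × √(1/1080 + 1/1350) = 0.0408 × SD.

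**Effect of adjustment.** With correlation r between prior-year and 3-year cost and a linear covariate, adjusted SE = SE × √(1 − r²).
- r = 0.3: √0.91 = 0.954, a cut of about 5%; equivalent size 2430/0.91 = 2,670.
- r = 0.6: √0.64 = 0.80, a cut of 20%; equivalent size 2430/0.64 = 3,797.

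Both SD and r are assumptions. In euros, with 95% half-widths (1.96 × SE) in brackets:

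| Assumed SD | Unadjusted | r = 0.3 | r = 0.6 |
|---|---|---|---|
| 5,000 | 204 (400) | 195 (382) | 163 (320) |
| 10,000 | 408 (800) | 389 (763) | 327 (640) |
| 20,000 | 816 (1,600) | 779 (1,527) | 653 (1,280) |

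**Share of the error due to prior-cost imbalance.** This part has standard deviation r × SE: EUR 122 (SD 10,000, r 0.3), 245 (10,000, 0.6; also 20,000, 0.3) and 490 (20,000, 0.6). The probability that it alone exceeds EUR 317 in either direction is about 1%, 20% and 52% respectively.

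**What does not carry over.** These results are for the cost difference. The INMB also contains QALYs multiplied by a willingness-to-pay value. The article gives neither the value nor a QALY SD, so the gain for the INMB cannot be computed.

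**The case against.** The strongest reply is that this is ordinary sampling error. Patients are randomised and analysed by intention to treat, so the unadjusted cost difference is unbiased, and the bootstrap interval, acceptability curves and value-of-information analysis exist to express such uncertainty. That stands, and it limits the point to precision.

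Three stronger readings are tempting, and the document supports none of them.

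- A reader might infer that chance imbalance in prior spending will overwhelm the statin saving. That depends on an SD and a correlation that the article does not give. It is unlikely at SD 10,000 and r 0.3, and plausible only at higher values. Adjustment would not remove the problem either, because most of the noise is not prior spending: with SD of EUR 10,000 or more and r up to 0.6, the adjusted SE is still about as large as the saving or larger.
- A reader might infer that the linkage can supply prior cost for nearly every patient. The 98.8% is coverage of the French population, not the trial's linkage rate, and the article does not say that data from before randomisation are requested or authorised. Its silence on the extraction window is not an error, since an article commonly leaves that to the full protocol.
- A reader might take the unstratified allocation as a fault. It means only that the design balances no proxy for prior spending; randomisation remains valid without it.

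It could also be said that covariates belong in an analysis plan that is not shown. That has less force here, because the article names the INMB covariates itself.

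**Conclusion.** The point holds as a cheap gain in precision for the cost component of a main objective. The stated covariate list covers statin use only, and no adjustment is named for the cost/utility ratio. Under assumed correlations of 0.3 to 0.6, adding prior-year cost would reduce the SE of the cost difference by about 5% to 20%. It would not settle the direction of the cost difference: even at an assumed SD of EUR 5,000 with r 0.6, the 95% half-width of EUR 320 is about the size of the drug saving. The conclusion rests on an assumed SD and correlation, on a linear covariate effect, and on prior-year data being obtainable. No bias in the planned estimates is claimed.

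**What to change.** Subject to confirming that the data-access authorisation covers it:

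1. Extend the SNDS request to the 12 months before each patient's randomisation date.
2. Prespecify total cost in those 12 months as a covariate in the cost and INMB regressions, and fix its functional form in advance. The gains above are for a linear term; a log or categorised form may give a different gain.
3. Refit the adjusted model in each bootstrap replicate, so that the cost/utility ratio and the acceptability curves use the same adjusted incremental cost.
4. Handle patients without prior-year data by a missing indicator or mean imputation. Either is acceptable for a baseline covariate in a randomised comparison. It does not deal with missing follow-up costs.
5. Report the unadjusted estimate alongside.

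The cost is one more year of data in the extraction request and one more covariate. No additional patients or visits are needed.

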### Safety and adverse event reporting

The adverse events expected during this research are mainly those related to the age of the study population, such as CV events, diabetes mellitus and/or its complications, cognitive disorders and dementia, falls, cancers, deaths, and adverse effects of concomitant therapies. Given that one group of patients will continue to use statins, adverse reactions listed in the summaries of product characteristics are also expected.

The Sponsor unit charged with security and vigilance must be informed immediately of any serious adverse events (SAEs), regardless of whether expected or unexpected, via the eCRF. This ensures continuous monitoring of safety of patients included throughout the trial. Moreover, annual safety evaluations will be conducted by the security and vigilance unit of the Sponsor, with particular focus on CV morbidity and all-cause mortality in both groups. The Data Safety Monitoring Board (DSMB) of the study will meet when 50% of the patients reach 12 and 24 months of follow up. We did not anticipate criteria by which the trial may be stopped, but the advice of the DSMB could be solicited in the case of unexpected safety issues or new information. In addition, all CV events will be validated by an external adjudication committee, which includes a cardiologist, a neurologist, and an internal and a geriatric medical specialist.

The Sponsor’s security and vigilance unit must communicate serious unexpected adverse reactions (SUSARs) and new information in the research in a timely manner in accordance with current regulations:
To the French National Agency for the Safety of Medicines and Health Products, (Agence Nationale de Sécurité du Médicament et des Produits de Santé (ANSM)).To the research ethics committee (Comité de Protection des Personnes (CPP)). The committee will ensure, if necessary, that the research participants were informed about the side effects and confirm their consent.

On the anniversary date of first inclusion, the security and vigilance unit prepares an annual safety report including:
A list of serious side effects of the researchA concise and critical analysis of the safety of participants in the research

This report is sent to the ANSM and the CPP within 60 days of the anniversary date of first inclusion.

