### Trial management

The scientific committee (SC) is composed of the coordinating investigator, Sponsor representatives, pharmacist, statistician, general practitioner, cardiologist, and geriatrics and experts in the field. The frequency of the SC meeting is at least once a year as needed during the research. The SC provides overall supervision of the trial; it will ensure that the study is carried out appropriately, scientifically, clinically and ethically. The SC is the decision-making executive body for all issues related to the trial implementation or follow up.

The DSMB is composed of six experienced external experts in the field of general practice, cardiology, geriatric medicine, methodology, and pharmacy, and are all nominated by the trial Sponsor. The DSMB is a consultative board for the SC and the Sponsor. It monitors the main safety and efficacy outcome measures and the overall conduct of the trial, with the aim of protecting the participants’ safety and interests. The DSMB will meet when 50% of the participants reach 12 and 24 months of follow up.

The day to day activities are supervised by a project coordination team that meets every 3 months and refers to the SC. The events validation committees will be in charge of validating neurovascular and cardiovascular events that occur during the course of the trial. This committee will meet to validate clinical events before the DSMB meeting to ensure that the results provided to the DSMB are consolidated.

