## Trial status

Patient recruitment started on 15 June 2016. The expected recruitment completion date is 31 December 2019.

The protocol version number is 8.0, dated 5 June 2019.

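### No mortality criterion is set for a trial that withdraws a preventive drug with death as primary endpoint; separately, the first scheduled DSMB meeting comes late in recruitment

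*Protocol article*

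**What the plan says.** Under Safety and adverse event reporting, the Protocol article states: "We did not anticipate criteria by which the trial may be stopped". It adds that DSMB advice "could be solicited in the case of unexpected safety issues or new information". The same section lists the adverse events that are expected in this age group, and the list includes "falls, cancers, deaths, and adverse effects of concomitant therapies".

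The DSMB "will meet when 50% of the patients reach 12 and 24 months of follow up". Under Trial management its remit is wide: "It monitors the main safety and efficacy outcome measures and the overall conduct of the trial". It is made up of six external experts and is consultative to the scientific committee and the sponsor.

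Three further routes are described under Safety and adverse event reporting:
- Serious adverse events are reported to the sponsor's vigilance unit immediately.
- "annual safety evaluations will be conducted by the security and vigilance unit of the Sponsor", with a focus on cardiovascular morbidity and all-cause mortality in both groups.
- An annual safety report goes to the national medicines agency (ANSM) and the ethics committee (CPP).

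Under Trial status, recruitment began on 15 June 2016 and "The expected recruitment completion date is 31 December 2019". Under Timeline and recruitment, the recruitment period is 36 months.

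**The concern.** There are two separate weaknesses, and neither causes the other.

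**No criterion.** The DSMB is asked to monitor the main safety outcomes but is given no guideline for the one that matters most. The article does not defer the question to a charter; it says that criteria were not anticipated. The ad hoc route does not clearly fill the gap. It is optional and tied to unexpected issues, whereas an excess of deaths is an excess of a listed expected event. The trial is open-label, so a criterion chosen after mortality by group is known would be hard to defend.

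**Late first meeting.** The first scheduled review by the DSMB waits until half the patients have 12 months of follow-up. By then most participants are likely to have been randomised, so a recommendation on recruitment would affect few of them.

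At stake is participant protection and the credibility of any decision to stop or continue. The final non-inferiority test is not in question.

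**Working it through.** **Inputs from the Protocol article:** 1080 cessation and 1350 continuation; 15% three-year mortality in both groups; margin 5 points; one-sided 2.5%; 90% power; recruitment 15 June 2016 to 31 December 2019 (42.5 months) or 36 months. **Assumptions not in the article:** uniform accrual and exponential mortality.

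**1. The plan's own sample size.** n = 2 × 0.15 × 0.85 × (1.960 + 1.282)² / 0.05² = 1072 per group, against 1080 stated (0.7% apart). 1080 / 0.80 = 1350, total 2430. The inputs reproduce the plan.

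**2. Timing, with 50% read as half of the planned 2430.** With recruitment period R, the meetings fall at R/2 + 12 and R/2 + 24 months.
- R = 42.5: first meeting at month 33.3, share randomised 33.3 / 42.5 = 78% (about 1,901).
- R = 36: first meeting at month 30, share 30 / 36 = 83% (2,025).
- The second meeting falls at month 45.3 or 42, after recruitment ends in both cases.
- With cumulative accrual (t/R)^k and k from 0.7 to 2, the share at the first meeting is 74% to 98% (R = 42.5) or 78% to 100% (R = 36).

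**3. Timing, with 50% read as half of those enrolled to date.** Under uniform accrual (t − 12)/t = 0.5 gives t = 24 months. The share is 24 / 42.5 = 56% or 24 / 36 = 67%.

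**4. Deaths at each meeting (R = 42.5, reading of step 2).** Monthly hazard λ = −ln(0.85)/36. A patient enrolled at month e has died by month t with probability 1 − exp(−λ × HR × min(t − e, 36)), with HR applied to cessation only. An excess at the margin (20% v 15%) is HR = ln(0.80)/ln(0.85) = 1.37.

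**5. Chance of crossing one-sided p<0.001.** Φ( ln(HR) × √(D × 4/9 × 5/9) − 3.09 ), where D is the number of deaths expected under that HR.

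| HR | Deaths, first | Excess | Crossing | Deaths, second | Excess | Crossing |
|---|---|---|---|---|---|---|
| 1.0 | 135.8 | 0 | 0.1% | 236.9 | 0 | 0.1% |
| 1.37 | 156.8 | 21.0 | 13% | 272.9 | 36.0 | 31% |
| 1.6 | 169.3 | 33.5 | 48% | 294.0 | 57.1 | 82% |
| 2.0 | 190.5 | 54.7 | 95% | 329.8 | 92.9 | over 99% |

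Example, HR 1.6 at the first meeting: 0.470 × √(169.3 × 20/81) = 3.04, and Φ(3.04 − 3.09) = 48%. Putting the 136 deaths expected under no effect into the formula would give only about 36% for HR 1.6 and 82% for HR 2.0. The count under each HR is the right one, because a harmful effect brings more deaths.

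**6. False alarms when HR = 1.** 0.1% per look; at most 2 × 0.1% = 0.2% for two looks, and 0.3% to 0.4% with one or two added looks.

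**The case against.** The strongest reply is that this is a declared choice: six external experts are to judge mortality without a formula, and nothing else in the article contradicts that. It is true that no other passage conflicts and no planned analysis changes. It does not follow that the choice is a good one. A non-binding guideline leaves the board's judgement intact and fixes in advance what would count as alarming.

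Several stronger readings are tempting, and the article does not support them:
- **That only the sponsor reviews safety before the first DSMB meeting.** The annual safety report goes to the ANSM and the CPP, both outside the sponsor. It is not said to give mortality by group or to carry a threshold, but external oversight exists.
- **That 78% randomised at the first meeting is a fact of the plan.** It rests on the Trial status dates, uniform accrual and one reading of 50%. Under uniform accrual the range is 56% to 83%.
- **That the design accepts 5 extra deaths per 100.** The upper 95% bound must lie below 5 points. At 15% mortality with 1080 and 1350 patients the standard error is √(0.15 × 0.85 × (1/1080 + 1/1350)) = 1.46 points, so the observed difference must be below about 5 − 1.96 × 1.46 = 2.1 points.
- **That a p<0.001 guideline would catch an excess at the margin.** It would usually stay silent there (13% and 31%).
- **That independent review could have begun at the first anniversary.** That date (mid-2017) had passed before protocol version 8.0 of 5 June 2019. Only about 18 deaths would have been expected by then, too few for a threshold to do much.

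The timing objection has real force. With the Trial status dates and uniform accrual, the two scheduled meetings fall at about March 2019 and March 2020, both before the article appeared in April 2020. What stands is the value for the remaining follow-up, which for the last patients runs to about the end of 2022.

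**Conclusion.** The point holds and should be acted on. The plan states that it has no stopping criteria, and none of the other safeguards described supplies a mortality threshold. This is a weak choice where the intervention withdraws a preventive drug and death is the primary clinical endpoint.

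The late first meeting is a second, separate weakness. On either reading of 50%, under uniform accrual, more than half of the participants are randomised before it.

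A harm-only guideline would be useful against large harm and weak against an excess at the margin, where DSMB judgement remains essential. These probabilities assume uniform accrual, exponential mortality at the plan's 15% and a constant hazard ratio. With a 36-month recruitment period they barely move: 46% and 94% at the first meeting for HR 1.6 and 2.0, and 12% at the margin. An unseen DSMB charter could contain more, but the article does not point to one for this purpose.

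**What to change.** Under Safety and adverse event reporting, replace the sentence on stopping criteria with a non-binding, harm-only guideline for all-cause mortality at each DSMB review. One example is a one-sided p<0.001 for more deaths under cessation; the DSMB may choose another threshold. State that there is no early stopping for non-inferiority. A rule that can only stop for harm cannot raise the chance of a false non-inferiority claim, so the final 95% confidence-interval rule stays as it is. State also that the DSMB uses its judgement for excesses below the threshold.

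Send the annual evaluations of mortality in both groups to the DSMB for the remaining follow-up, and say whether 50% of participants refers to the planned number or to those enrolled to date.

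The cost is protocol and charter wording, and one or two further reviews by an existing board of evaluations already planned. The downside is a false-alarm risk of at most 0.2% for two looks, or 0.3% to 0.4% with the added ones.
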